Taken together, the existing retrospective and prospective data suggests that omitting PORT in patients with a pN0 neck likely has a recurrence rate less than 15–20%. However, no randomized studies have directly examined the omission of PORT in the pN0 neck. There is also a paucity of data examining the effects of omission of PORT on QoL. We hypothesize that omitting PORT to the hemi-neck(s) that have been dissected and shown to be pN0 will be associated with acceptable rates of regional recurrence and will improve quality of life (QoL). The goal of this randomized phase II study is to assess oncologic outcomes, functional outcomes, and QoL in patients treated with PORT to the historically standard volumes (usually including the primary site and all dissected neck areas) vs. PORT only to the primary site and pathologically involved hemi-neck, omitting radiation to the pN0 hemi-neck(s).

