#### Follow-up evaluation

Day 1 of follow-up will be the first day of radiotherapy. Follow-up will consist of history and physical examination with laryngopharyngoscopy, CT imaging of the neck ± thorax, QoL assessments and MBS. The follow-up schedule is shown in Additional file 2. Additional imaging or laboratory investigations should be carried out at the discretion of the oncologist, based on findings in the history or physical examination. Additional treatment (e.g. salvage treatment with surgery or further radiotherapy) is at the discretion of the treating physicians but will be recorded in the case report form.

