#### Measurement of outcomes

**pN0 neck failure:** measured as time from randomization until disease recurrence in the initially pN0 hemi-neck(s). Patients with prior or simultaneous recurrence at the primary site or in the initially pN+ hemi-neck will be censored for this outcome as of that timepoint. The primary endpoint is a comparison of pN0 neck failure in Arm 2 vs. historical controls; this endpoint will also be compared between the two arms as a secondary endpoint.**OS:** measured as time from randomization until death from any cause.**DFS:** measured as time from randomization to either recurrence at any location or death, whichever occurs first. New primary tumours will not count as DFS events.**Local recurrence:** measured as time from randomization until disease recurrence at the primary site.**Regional recurrence:** measured as time from randomization until disease recurrence anywhere in the neck.**Locoregional recurrence:** measured as time from randomization until disease recurrence anywhere in the neck or at the primary site, whichever occurs first.**Recurrence in the pN0 neck without other locoregional recurrence:** measured as time from randomization until disease recurrence in the pN0 neck alone without recurrence at the primary site or pN+ neck.**Rate of salvage surgery and/or radiation in pN0 neck:** measured as time from randomization to salvage intervention (surgery ± radiation) in the pN0 neck. Freedom from unsalvageable neck recurrence will be reported as the time from randomization to development of a neck recurrence in the pN0 neck that could not be salvaged.**Feeding Tube Insertion:** Rate of feeding tube insertion after start of radiation (either gastric, gastrojejeunal, or nasogastric) and rate of feeding tube use at 1-year post-randomization. Patients with feeding tubes inserted prior to randomization will be censored for this endpoint.**Rate of failure in the clinically node negative neck**: for patients who have unilateral neck dissections, the cN0 neck may be treated with radiation or observed, at the discretion of the treating oncologist (see section 6). This is measured as the time from randomization to failure in the cN0 neck, and will be reported for the whole group of patients who had unilateral dissections, and also stratified by whether radiation was delivered to that area.

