Utilities will be calculated from the EQ-5D-5L which will be administered at baseline and at 6 month intervals. Quality adjusted life years (QALYs) will be assessed as the area under the preference-weighted survival curve. Overall costs of each treatment strategy will be abstracted from the available literature. The incremental cost effectiveness ratios (ICERs) between treatment arms will be compared through the standard method of ratio between differences in costs and QALYs. Point estimates for these differences can be derived from multivariable generalized estimating equations (GEE) or generalized linear model (GLM) analyses.

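### The cost-effectiveness paragraph takes strategy-level costs from the literature but plans a multivariable GEE or GLM for the cost difference, and the two do not fit together

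*Protocol article*

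**What the plan says.** The last paragraph of the Analysis plan in the protocol article sets out the economic analysis.

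- **QALYs** come from trial patients: "Utilities will be calculated from the EQ-5D-5L which will be administered at baseline and at 6 month intervals".
- **Costs** come from outside the trial: "Overall costs of each treatment strategy will be abstracted from the available literature".
- **The ICER** is the difference in costs between arms divided by the difference in QALYs.
- **The model** for both differences follows: "Point estimates for these differences can be derived from multivariable generalized estimating equations (GEE) or generalized linear model (GLM) analyses".

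Elsewhere the article shows that events which drive cost are collected in the trial. Under Follow-up evaluation, salvage treatment "is at the discretion of the treating physicians but will be recorded in the case report form". Under Measurement of outcomes, the feeding-tube outcome is "Rate of feeding tube insertion after start of radiation (either gastric, gastrojejeunal, or nasogastric) and rate of feeding tube use at 1-year post-randomization". Toxicity is a secondary endpoint, and the Analysis plan compares grade 2 or higher events between arms. Use of concurrent chemotherapy is a stratification factor. The economic paragraph links none of these to costs.

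**The concern.** The unit being costed is the strategy, the cost is an overall one, and its source is published work. A cost of that kind depends on arm alone. Two things follow.

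First, the paragraph conflicts with itself. A multivariable regression of cost needs an outcome that varies between patients, and a strategy-level cost does not supply one.

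Second, the ICER would divide an external cost difference by a QALY difference measured in the trial. Table 1 and the Radiotherapy planning section give both arms 30 fractions with the same permitted techniques. A real cost difference should therefore arise mainly downstream, from neck salvage, feeding tubes and toxicity care. The trial measures these events, yet a strategy-level literature cost does not respond to them. If omission led to more salvage, or to less toxicity care, the numerator would not show it.

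**Working it through.** **Figures in the plan.** The economic paragraph states none. The illustration below borrows the design figures in the Sample size section: 30 and 60 patients, and pN0-neck control of 92% or 80%. Those figures reproduce. With 60 × 0.95 = 57 evaluable patients, the exact binomial rule needs at least 51 controlled, giving one-sided alpha 0.045 and power 0.831, against the stated 83.1%. The present point does not depend on that calculation.

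**Step 1: can GEE/GLM estimate a cost difference from strategy-level costs?** Let every Arm 1 patient have cost C1 and every Arm 2 patient cost C2. Regressing cost on arm gives a coefficient of exactly C2 − C1, all residuals are zero, and covariates have nothing left to explain. As a check, costs of 10 for 30 patients and 9 for 60 patients gave a coefficient of −1, with standard error and residual variance both zero to rounding. The model returns the input figures and nothing more. For QALYs, which vary between patients, it works as intended.

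**Step 2: what sampling error would patient-level costs carry?** Assume the same mean cost and coefficient of variation (CV) in each arm. As a fraction of mean cost, the standard error (SE) of the difference is

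SE = CV × √(1/30 + 1/60) = CV × 0.2236

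| Assumed CV | SE (% of mean cost) | 95% half-width |
|---|---|---|
| 0.3 | 6.7% | 13% |
| 0.5 | 11.2% | 22% |
| 1.0 | 22.4% | 44% |

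A fixed cost per arm gives 0 in every row.

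**Step 3: how large could the salvage component be?** Let S be the cost of one salvage episode, and p1 and p2 the salvage rates in Arms 1 and 2.

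Difference = (p2 − p1) × S; SE = S × √[p1(1 − p1)/30 + p2(1 − p2)/60]

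The p2 values of 8% and 20% are the complements of the 92% and 80% control rates and assume that every failure is salvaged. The p1 values are assumptions.

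| p2 | p1 | Difference | SE |
|---|---|---|---|
| 8% | 2% | 0.06 S | 0.043 S |
| 8% | 5% | 0.03 S | 0.053 S |
| 8% | 8% | 0 | 0.061 S |
| 20% | 2% | 0.18 S | 0.058 S |
| 20% | 5% | 0.15 S | 0.065 S |
| 20% | 8% | 0.12 S | 0.072 S |

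For example, with p2 = 8% and p1 = 2%: √(0.02 × 0.98/30 + 0.08 × 0.92/60) = √(0.000653 + 0.001227) = 0.043.

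Salvage is only one component. Less feeding-tube use or toxicity care in Arm 2 would move the difference the other way, so the net sign is open.

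**The case against.** The strongest reply is that the sentence on costs is terse and stands in a condensed article. It does not say how many literature figures will be used, and it does not exclude published unit costs applied to recorded events. The mention of multivariable models may even suggest that patient-level values were intended. Costing detail commonly sits in a fuller document. This stands as far as it goes: that each arm gets exactly one figure is an inference. But the point rests on what the paragraph states, not on detail it leaves out. Its wording assigns an overall cost to a strategy, and that does not fit the model named two sentences later. If patient-level costing was intended, the sentence still needs correcting.

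Several stronger readings are tempting, and the documents do not support them:

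- *The ICER would be wrong.* Literature-based costing is an accepted, if weaker, approach, and without any cost figure no error can be shown.
- *The ICER would be zero, hiding the cost of salvage.* That needs equal delivery costs in both arms. The article speaks of overall costs and does not say they are equal.
- *The plan reports a zero standard error, or understates uncertainty.* The paragraph promises point estimates only. Zero sampling error follows only if the costs are treated as fixed, and literature ranges could be used in a sensitivity analysis.
- *No literature cost can exist for Arm 2.* The Background says "no randomized studies have directly examined the omission of PORT in the pN0 neck". That concerns efficacy evidence. Published costs of radiotherapy, salvage or feeding tubes do not need a randomized omission trial.

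It is also fair to say that the Step 3 figures rest on assumed rates. Failure is not the same as salvage, since the article defines unsalvageable neck recurrence separately. At 8% in Arm 2 the salvage-driven difference is about the size of its standard error or smaller, so trial-based costing might not separate the arms on that item.

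**Conclusion.** The point holds as a mismatch between the stated cost source and the stated model. On the plain reading, GEE/GLM can serve QALYs but not costs, and the ICER would not reflect the downstream events of this trial. If the costs are treated as fixed, the cost difference has no sampling error, against an illustrative 6.7% to 22.4% of mean cost for patient-level costs with CV 0.3 to 1.0. The CVs, the Arm 1 salvage rates and the equating of failure with salvage are assumptions. The size and direction of any error in the ICER cannot be computed from the documents.

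Severity is low. Cost-effectiveness appears in neither the Objectives nor the Secondary endpoints list, and the primary conclusion and sample size do not depend on it.

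**What to change.** Replace the sentence on costs with:

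> Published unit costs will be applied to each patient's recorded resource use (radiotherapy, concurrent chemotherapy, salvage surgery or radiation, feeding tubes, and care of grade 2 or higher toxicity as recorded). Cost and QALY differences will be estimated from these patient-level values, with ICER uncertainty obtained by bootstrapping cost and QALY jointly within arm.

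Toxicity should not be limited to serious adverse events. Costing salvage while leaving out grade 2–3 toxicity care would tilt the result against Arm 2.

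If patient-level costing is not feasible, restrict GEE/GLM to QALYs and label the ICER a literature-costed estimate with sensitivity ranges.

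The price is some extra analysis work and a wider ICER interval. Salvage, feeding tubes, toxicity and chemotherapy use are already collected. The article describes toxicity by grade, so a published cost per graded event may have to stand in for the care actually given.

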#### Data safety monitoring committee

The Data Safety Monitoring Committee (DSMC), consisting of at least one radiation oncologist and one medical oncologist not involved in the study, will meet every 6 months after study initiation. Toxicity outcomes will be monitored, but since the experimental arm involves smaller radiation volumes, it is extremely unlikely that toxicity would be higher in the experimental arm, and therefore no stopping rules for toxicity are included.

##### Interim analysis

The DSMC will conduct one interim analysis once 45 patients have been accrued and completed the 6-month QoL questionnaires. For this analysis, the DSMC will be blinded to the identity of each treatment arm, but QoL, recurrence in the pN0 neck, OS, and DFS estimates at 2-years will be presented for each arm.

The DSMC will recommend stopping the trial if there is an OS difference that is statistically significant with a threshold of *p* < 0.001 using the stratified log-rank test, based on the Haybittle-Peto stopping rule; this retains an overall alpha of 0.05.

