### Study design

This is an open-label phase II multi-centre randomized trial. Patients will be randomized between current standard of care treatment (Arm 1) vs. omission of radiation to the pN0 dissected hemi-neck(s) (Arm 2) in a 1:2 ratio (Fig. 1). The required sample size is 90 patients. Stratification factors include neck nodal status (pN0 vs pN+) and use of chemotherapy. Patients will be recruited from tertiary care centres (full list of participating sites available on clinicaltrials.gov, NCT03997643).

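### The only written stopping criterion, OS at p<0.001, protects little against plausible harm in Arm 2, and pN0-neck failure, the primary endpoint, has no trigger

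*Protocol article*

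**What the plan says.** The section on the data safety monitoring committee has the DSMC meet every 6 months. It reasons that "since the experimental arm involves smaller radiation volumes, it is extremely unlikely that toxicity would be higher in the experimental arm". On that ground it waives any such rule: "therefore no stopping rules for toxicity are included".

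The Interim analysis section provides "one interim analysis once 45 patients have been accrued and completed the 6-month QoL questionnaires". At that look "the DSMC will be blinded to the identity of each treatment arm, but QoL, recurrence in the pN0 neck, OS, and DFS estimates" are to be shown by arm, for the 2-year point. A single criterion follows: "The DSMC will recommend stopping the trial if there is an OS difference that is statistically significant with a threshold of". The cut-off given is p<0.001 by stratified log-rank, attributed to Haybittle-Peto, and overall alpha is said to stay at 0.05.

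Study design sets "omission of radiation to the pN0 dissected hemi-neck(s) (Arm 2) in a 1:2 ratio", so 45 patients split about 15 to 30. The Sample size section treats a 2-year pN0-neck failure risk of 20% in Arm 2 as the level to exclude. The document gives no boundary, count or guideline for that endpoint during the trial.

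**The concern.** Leaving radiation out of a dissected neck is unlikely to raise toxicity, and the protocol says so. The harm to expect is recurrence in that neck. The written criterion instead watches OS, which responds later (salvage is anticipated and recorded) and is tested when few deaths can have occurred. It is also less sensitive in the direction that matters, because the arm at risk of harm is the larger one.

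At stake is how soon a clearly unsafe omission would be acted on while two of every three new patients are allocated to it. Arm 2 could already have lost its primary hypothesis with no written rule prompting a decision.

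**Working it through.** **1. The plan's own figures.** Inputs from Sample size: 60 patients in Arm 2, 5% dropout, control of 92% against 80%, one-sided 0.05. n = 60 × 0.95 = 57. With X the number of failures:
- P(X ≤ 6 | 57, 0.20) = 0.045, the type I error.
- P(X ≤ 6 | 57, 0.08) = 0.831, which reproduces the stated 83.1%.

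Haybittle-Peto with an interim two-sided 0.001 and an unadjusted final 0.05 gives an overall alpha of 0.0502-0.0508 for information fractions of 0.1-0.5. The alpha statement is right to rounding.

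**2. Most extreme split under the OS rule.** Sidedness is not stated; two-sided is assumed, so |Z| must exceed 3.29. Take 15 against 30 at risk, no censoring, unstratified, all deaths in one arm, and Z = (O − E)/√V summed over deaths.
- 15 deaths, all Arm 2: (15 − 9.00)/√3.568 = 3.18, no stop.
- 16 deaths, all Arm 2: (16 − 9.50)/√3.818 = 3.33, stop.
- 5 deaths, all Arm 1: (5 − 1.51)/√1.050 = 3.41, stop.

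**3. Deaths needed for 80% power at p<0.001.** Schoenfeld: D = (3.29 + 0.84)² / [(1/3)(2/3)(ln HR)²]. This gives 160 deaths at HR 2, 64 at HR 3 and 40 at HR 4. The look has 45 patients.

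**4. Chance that the rule fires for harm in Arm 2.** The protocol gives no OS rate, accrual time or hazard ratio, so all three are assumed. Survival is exponential, and the look falls when the last of the 45 reaches 6 months.

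| Arm 1 2-year OS | Accrual of the 45 | HR | Chance of stopping |
|---|---|---|---|
| 70-80% | 12-30 months | 2 | under 1% |
| 70-80% | 12-30 months | 3 | about 0.3-7% |
| 65% | 36 months | 4 | about 27% stratified, 34% unstratified |

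A repeat of the HR 3 row with uniform accrual (6,000 trials per cell, unstratified) gave 0.05% to 5.5%. The lower end is therefore soft, but the conclusion is the same.

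**5. When the primary test is lost.** P(X ≤ 7 | 60, 0.20) = 0.067, above 0.05. At n = 57 it is 0.093, and it rises as n falls. No n up to 60 tolerates more than 6 failures.

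**6. Chance of 7 or more among 30 Arm 2 patients by the look.** Assume constant hazard h = −ln(1 − p)/24 per month for a true 2-year rate p, and entry uniform over A months. Failures count up to 24 months, so each patient's chance is q = (1/A)∫ from 6 to A+6 of [1 − exp(−h·min(u, 24))] du. Competing events are ignored; they would lower these figures.

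| True 2-year rate | A = 12 | A = 30 | Full 2-year follow-up |
|---|---|---|---|
| 8% | 0.02% | 0.2% | 0.8% |
| 20% | 3.3% | 18.3% | 39% |
| 30% | 20.3% | 59.6% | 84% |

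Slightly different treatment of accrual moves the interim figures by about a point (3-19% at 20%, 21-59% at 30%).

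**7. Why the 24-month limit matters.** At a true 2-year rate of 8% and constant hazard, the 3-year rate is 1 − 0.92^1.5 = 11.8%. The chance of 7 or more failures in 60 by then is about 57%, although the 2-year test may succeed.

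**The case against.** The protocol misstates nothing here: its power and alpha figures reproduce, and Haybittle-Peto is conservative by design. DSMC guidance often sits in a charter, and this is a condensed article. The DSMC meets every 6 months and is shown pN0-neck recurrence by arm at the interim. The text says when it will recommend stopping, not that OS is the only permitted ground. All of this stands. It limits the point to the absence of a written trigger on the primary endpoint beside an explicit but insensitive one on OS.

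A reader might go further in several ways that the document does not support:
- **That the OS rule can never fire.** At HR 4 with poor survival and slow accrual it fires in about a quarter to a third of trials.
- **That the 1:2 ratio defeats the DSMC's blinding.** The display format is not stated; arms are identifiable only if denominators or numbers at risk are shown.
- **That 2-year estimates cannot be computed at the look.** Six months is the minimum follow-up. With slow accrual, early patients pass 2 years and estimates exist, though they are imprecise.
- **That the plan claims a safeguard it lacks, or compels continued randomization.** The OS rule is never offered as a guard against neck recurrence, and discretion remains.
- **That the 39% and 84% chances describe the interim.** They need all 30 patients followed for 2 years.

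**Conclusion.** The point holds as a cheap improvement to monitoring, not as an error in the protocol. The sole written criterion gives little protection against plausible harm in Arm 2: about 0.3-7% at HR 3 and under 1% at HR 2, on assumed survival and accrual and a two-sided threshold. The 16-of-30 figure is for an unstratified test without censoring, while the plan specifies a stratified one.

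The endpoint that carries the foreseeable harm has no trigger, although its data already reach the DSMC and the design implies a natural count. The seventh qualifying failure needs no survival assumption: it follows from the protocol's own test. By the interim it would be reached rarely at a true rate of 8%, and in roughly one to three trials in five at 30%.

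**What to change.** Add to the Interim analysis section or the DSMC charter:

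- At each 6-monthly meeting, the DSMC counts Arm 2 pN0-neck failures that occur within 24 months of randomization and qualify under Measurement of outcomes, that is, not after or simultaneous with recurrence at the primary site or in the pN+ hemi-neck.
- At the seventh such failure, accrual pauses and the DSMC recommends whether to continue.
- The DSMC is given arm identity for this count, because the trigger is specific to Arm 2.
- Event counts and 6- and 12-month cumulative incidence are shown beside the 2-year estimates.
- The OS rule stays.

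The cost is wording only; the meetings and data exist. With both limits on what is counted, the trigger adds no type I error and loses no primary-test power. At a true rate of 8% with all 60 followed for 2 years it would be reached in 20% of trials (1 − 0.798), exactly those that would miss the primary test anyway. The one downside is that a pause could reduce numbers for secondary comparisons such as MDADI at 1 year.

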#### Ethical considerations

The Principal Investigator will obtain ethical approval and clinical trial authorization by competent authorities according to local laws and regulations. The World Health Organization (WHO) Trial Registration Data Set is shown in Additional file 4.

##### Institutional review board (IRB) / research ethics board (REB)

The protocol (and any amendments), the informed consent form, and any other written information to be given to subjects will be reviewed and approved by a properly constituted IRB/REB operating in accordance with the current federal regulations (e.g., Canadian Food and Drug Regulations (C.05.001); US Code of Federal Regulations (21CFR part 56)), ICH GCP and local regulatory requirements. A letter to the investigator documenting the date of the approval of the protocol and informed consent form will be obtained from the IRB/REB prior to initiating the study. Any institution opening this study will obtain IRB/REB approval prior to local initiation.

